### Comparison between CIAT Plus and M-MAT groups WAB-R-AQ

A longitudinal linear mixed model will be used to assess the difference between the CIAT Plus and M-MAT groups on WAB-AQ immediately post intervention and at 12 weeks follow-up. The interaction effect: *group × baseline severity* will be included in the model to assess the effects of CIAT Plus and M-MAT on participants with different baseline severity classifications. The between-group difference at each time point will be assessed through the *group× time* interaction effect. The model will adjust for baseline aphasia severity by including the WAB-AQ at baseline as a covariate. Baseline stroke severity will be controlled for by including mRS at baseline as a fixed factor in the model. The treatment group will be included as a random effect.

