## Introduction

Aphasia is an acquired language disability, impacting all aspects of communication underpinned by language: speech, reading, writing, and speaking. Aphasia is present in approximately one third of stroke survivors [1], with significant negative impacts on mental health [2] and quality of life [3]. The 2016 Cochrane review of speech and language therapy for aphasia after stroke analysed 57 aphasia therapy trials and showed statistically significant treatment effects immediately after intervention but not at follow-up [4]. Although there is a broad range of approaches to aphasia intervention there is extremely limited evidence concerning their differential effects [4]. Two commonly utilised therapies, Constraint-induced Aphasia Therapy Plus (CIAT Plus) [5] and Multi-modality Aphasia Therapy (M-MAT) [6] are both intensive, high-dose interventions aimed at improving verbal communication. However, they are hypothesised to rely on different underlying neural recovery mechanisms and importantly may be differentially effective based on overall aphasia severity. Determining the most effective intervention for sub-groups of patients with aphasia may lead to improved patient outcomes and reduced health care costs.

COMPARE is a prospective, assessor-blinded, randomised clinical trial with a group- randomised design, operating in community sites across Australia and New Zealand. The primary aim of the COMPARE trial is to determine whether two contrasting, intensive treatments for chronic post-stroke aphasia, CIAT Plus and M-MAT, are superior to non-standardised, limited aphasia therapy in the community (usual care: UC). The primary endpoint is improvement on the WAB-R-AQ [7] at therapy completion. A range of other aims are addressed through secondary hypotheses listed below. Ethics and local governance approval were obtained from all hospital and university sites supporting recruitment. Version 5.2 of the protocol, dated 7 May 2019, is current and the study protocol has been published [8].

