### Randomisation

Eligible participants are randomised to one of three arms: CIAT Plus, M-MAT, or UC. The intervention protocol requires therapy to be provided face-to-face, in groups of three participants. The members of a treatment group therefore need to be in the same geographic location. The trial uses a stratified group-randomisation strategy. Once enrolled in the trial, participants are allocated to treatment groups based on their aphasia severity (WAB-R-AQ mild = 93.7–62.6; moderate = 62.5–31.3; severe < 31.3). The groups are then randomised to one of three arms (M-MAT, CIAT Plus or UC) in a 1:1:1 ratio via a central allocation system using blocked randomisation within each stratum.

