#### Secondary hypotheses

The following secondary hypotheses will be assessed:
Compared to UC, CIAT Plus and M-MAT will result in a reduction in aphasia severity on the WAB-R-AQ [7] at 12-week follow-up.Compared to UC, CIAT Plus and M-MAT will result in significantly more accurate and efficient connected speech (CIUs [9] per minute) immediately post intervention and at 12-week follow-up.Compared to UC, CIAT Plus and M-MAT will result in significantly better functional communication (CETI [10]) immediately post intervention and at 12-week follow-up.Compared to UC, CIAT Plus and M-MAT will result in significantly better multimodal communication (Scenario Test [11]) immediately post intervention and at 12-week follow-up.Compared to UC, CIAT Plus and M-MAT will result in a significantly better quality of life (SAQOL-39 [12]) immediately post intervention and at 12-week follow-up.M-MAT will be more effective in reducing aphasia severity (WAB-R-AQ [7]) immediately post intervention and at the 12-week follow-up than CIAT Plus for mild and severe aphasia, whereas CIAT Plus will be more effective than M-MAT for moderate aphasia.

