#### Secondary statistical hypotheses

The specified set of secondary effectiveness hypotheses involve the assessment of the following statistical hypotheses:
1.1.CIAT Plus will result in greater reductions in aphasia severity than UC, as measured by the WAB-R-AQ [7], at 12 weeks post stroke.1.2.M-MAT will result in greater reductions in aphasia severity than UC, as measured by the WAB-R-AQ [7], at 12 weeks post stroke.2.1.CIAT Plus will result in better efficiency of connected speech than UC, measured by CIUs/min [9], immediately post intervention and at 12 weeks follow-up.2.2.M-MAT will result in better efficiency of connected speech than UC, measured by CIUs/min [9], immediately post intervention and at 12 weeks follow-up.3.1.CIAT Plus will result in better functional communication than UC, measured by the CETI [10], immediately post intervention and at 12 weeks follow-up.3.2.M-MAT will result in better functional communication of connected speech than UC, measured by the CETI [10], immediately post intervention and at 12 weeks follow-up.4.1.CIAT Plus will result in better multimodal communication than UC, measured by the Scenario Test [11], immediately post intervention and at 12 weeks follow-up.4.2.M-MAT will result in better multimodal communication than UC, measured by the Scenario Test [11], immediately post intervention and at 12 weeks follow-up.5.1.CIAT Plus will result in better quality of life than UC, measured by the SAQOL-39 [12], immediately post intervention and at 12 weeks follow-up.5.2.M-MAT will result in better quality of life than UC, measured by the SAQOL-39 [12], immediately post intervention and at 12 weeks follow-up.6.1.For participants with severe aphasia at baseline, M-MAT will result in greater reduction in aphasia severity than CIAT Plus, as measured by the WAB-R-AQ [7], immediately post intervention and at 12 weeks follow-up.6.2.For participants with moderate aphasia at baseline, CIAT Plus will result in greater reduction in aphasia severity than M-MAT, as measured by the WAB-R-AQ [7], immediately post intervention and at 12 weeks follow-up.6.3.For participants with mild aphasia at baseline, M-MAT will result in greater reduction in aphasia severity than CIAT Plus, as measured by the WAB-R-AQ [7], immediately post intervention and at 12 weeks follow-up.

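### The CIAT Plus v M-MAT model names only group × baseline severity and group × time, so the band-by-time effects in hypotheses 6.1–6.3 rest on an untested assumption that the severity pattern is the same at both times

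*SAP article*

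**What the plan says.** Under Secondary hypotheses, M-MAT is predicted to be more effective "than CIAT Plus for mild and severe aphasia, whereas CIAT Plus will be more effective than M-MAT for moderate aphasia", both post intervention and at 12 weeks. The section Secondary statistical hypotheses splits this into 6.1 (severe), 6.2 (moderate) and 6.3 (mild), each stated for both times. Hypothesis 6.2, for example, reads: "For participants with moderate aphasia at baseline, CIAT Plus will result in greater reduction in aphasia severity than M-MAT".

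The section Comparison between CIAT Plus and M-MAT groups WAB-R-AQ sets out one longitudinal linear mixed model to compare the CIAT Plus and M-MAT "groups on WAB-AQ immediately post intervention and at 12 weeks follow-up". It names two interactions and gives each a job:

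- The group × baseline severity interaction "will be included in the model to assess the effects of CIAT Plus and M-MAT on participants with different baseline severity classifications".
- For the times: "The between-group difference at each time point will be assessed through the" group × time interaction.

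Baseline WAB-AQ and mRS enter as adjustments and the treatment group as a random effect. The section mentions no three-way interaction, no severity × time term, and no separate model for each time or band. The bands are those used at randomisation ("WAB-R-AQ mild = 93.7–62.6; moderate = 62.5–31.3; severe < 31.3").

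**The concern.** The hypotheses ask for six quantities. A model with group × severity and group × time gives the M-MAT minus CIAT Plus difference in a band at a time as a band part plus a time part. That is 3 + 2 − 1 = 4 free parameters for six contrasts. The gap between any two bands is therefore forced to be the same post intervention and at 12 weeks, and nothing in the stated model tests this.

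The hypothesised crossover makes the constraint matter. M-MAT minus CIAT Plus is predicted to be positive in mild and severe aphasia and negative in moderate aphasia. If these differences fade towards zero, the contrast falls in two bands and rises in the third. One common group × time shift cannot represent that. Part of the post-intervention pattern would be carried into 12 weeks, and the post-intervention pattern would be shrunk.

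Differential benefit by severity is a stated aim in the Abstract, and the Discussion there expects the results to inform individual choice of therapy. A wrong account of where and when one therapy is better would bear directly on that use.

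**Working it through.** The plan gives no figure for these contrasts, so there is none to reproduce. The check is what the stated model estimates on average when the truth is known.

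**Inputs from the SAP article**

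- Three bands and two outcome times (sections quoted above).
- A difference of 5 points, used here only as a scale (Sample size considerations). It is the plan's overall powering difference, not a band-specific effect.
- 216 participants, with groups randomised "in a 1:1:1 ratio via a central allocation system using blocked randomisation within each stratum", so 216/3 = 72 per arm. The plan's total reproduces: design effect 1 + (3 − 1) × 0.04 = 1.08, and 198 × 1.08 = 213.84, rounded up to a multiple of 3 = 216.

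**Assumptions not in the documents**

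- Band-specific effects, and band sizes (24 per arm per band unless stated).
- Complete data at both times.
- SD 10.25, which is what 198/3 = 66 per arm, 5 points, 80% power and two-sided 5% imply.
- Within-person correlation 0.7.

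**Formula.** With balanced times, the two-interaction model fits each cell as

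fitted(band, time) = band mean + time mean − grand mean.

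The error is therefore (change in that band − average change)/2 post intervention, and the opposite at 12 weeks. It is zero exactly when every band changes by the same number of points.

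**Full fade, equal bands.** Truth is +5/−5/+5 (mild/moderate/severe), then 0/0/0. Band means are 2.5, −2.5, 2.5; time means are 1.667 and 0; the grand mean is 0.833.

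- Mild and severe: post 2.5 + 1.667 − 0.833 = 3.33; 12 weeks 2.5 + 0 − 0.833 = 1.67.
- Moderate: post −2.5 + 1.667 − 0.833 = −1.67; 12 weeks −2.5 + 0 − 0.833 = −3.33.

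**Half fade, equal bands.** Truth is +5/−5/+5, then +2.5/−2.5/+2.5. Band means are 3.75, −3.75, 3.75; time means are 1.667 and 0.833; the grand mean is 1.25.

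- Mild and severe: post 3.75 + 0.417 = 4.17; 12 weeks 3.75 − 0.417 = 3.33.
- Moderate: post −3.75 + 0.417 = −3.33; 12 weeks −3.75 − 0.417 = −4.17.

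**Full fade, bands of 60/25/15%.** The post mean is 0.60 × 5 − 0.25 × 5 + 0.15 × 5 = 2.5 and the grand mean is 1.25. Moderate: post −2.5 + 1.25 = −1.25; 12 weeks −2.5 − 1.25 = −3.75.

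| Moderate band | True post | Fitted post | True 12 weeks | Fitted 12 weeks |
|---|---|---|---|---|
| Full fade, equal bands | −5 | −1.67 | 0 | −3.33 |
| Half fade, equal bands | −5 | −3.33 | −2.5 | −4.17 |
| Full fade, 60/25/15% | −5 | −1.25 | 0 | −3.75 |
| No fade | −5 | −5 | −5 | −5 |
| All bands shift by −3 | −5 | −5 | −8 | −8 |

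A generalised least squares calculation with the clustering (ICC 0.04) and within-person correlation included gives the same equal-band values. Adding severity × time alone does not change them. Adding group × severity × time recovers all six true values. The standard error per contrast then rises from 2.93 to 3.08 with 24 per arm in the band, and from 4.09 to 4.35 with 12 per arm (bands of 36/24/12).

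**The case against.** The strongest reply is that the section is prose and not a complete model formula. It does not spell out the main effects of group and time, or a participant-level random effect for repeated measures, so one unnamed term is weak evidence that the term is excluded. That has some force, and a one-line clarification might settle it. But the section does not merely stay silent: it assigns the severity question to one two-way interaction and the time question to another. An analyst who followed it would fit the constrained model.

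The second reply is that the hypotheses predict the same direction of effect in each band at both times. If the pattern persists at the same size, or there is no difference in any band at either time, the constrained model is correct and slightly more precise. That is true, but persistence is part of what the 12-week hypotheses are meant to examine, so the model should not assume it.

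Third, the +5/−5/+5 example with full fade is an invented and severe case. The half fade halves the error in the moderate band, from 3.33 to 1.67 points.

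Some stronger readings are tempting but not supported:

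- *That the six effects cannot be obtained.* The model does yield six estimates; they are tied together by the additivity constraint.
- *That any fading causes bias.* Bias needs the change to differ between bands. An equal shift in every band is absorbed by group × time.
- *That the Introduction shows fading will occur.* It says that a systematic review of aphasia therapy trials "showed statistically significant treatment effects immediately after intervention but not at follow-up". This concerns pooled therapy effects, and lack of significance is not a demonstrated fade to zero. It makes fading plausible for aphasia therapy in general and is not evidence about M-MAT v CIAT Plus within bands.

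**Conclusion.** The point holds as a mismatch between stated hypotheses and stated model. As written, the analysis estimates the six contrasts for 6.1–6.3 only under an untested equality of the severity pattern across the two times. Under the predicted crossover, any fade towards zero violates that equality. In the equal-band illustrations the moderate-band error is 1.67 points (half fade) to 3.33 points (full fade) at each time, in opposite directions, enough to make a shrinking effect look like a growing one. These sizes rest on assumed effects and band shares. That an opposite-sign pattern fading to zero distorts the time course does not depend on the exact values.

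A reader might infer that the trial's main result is at risk. It is not: the primary comparisons with usual care use a different model and are unaffected. Only secondary hypothesis 6 is concerned. The change should be made, but it is not critical to the trial's primary conclusion.

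**What to change.** Add severity × time and group × severity × time to the CIAT Plus v M-MAT model, and say explicitly that severity in these terms means the three randomisation bands. Fitting group × severity separately at each time is an acceptable alternative. Report the six band-by-time M-MAT minus CIAT Plus differences with 95% confidence intervals, and name these contrasts as the tests of 6.1–6.3. A joint group × severity test at each time is optional; by itself it does not test the directional, band-specific hypotheses.

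The cost is two extra parameters for the group contrast, two for severity × time, and slightly wider intervals: a half-width of about 1.96 × 3.08 = 6.0 points instead of 1.96 × 2.93 = 5.7, under the assumptions above. Precision within bands is low either way. Power for 5 points is about 37% with 24 per arm in a band and 21% with 12 (SD 10.25, design effect 1.08, assumed), so the report should give the intervals more weight than significance.

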### Handling of missing data

Missing data for secondary analyses will be handled as described in the section on treatment of missing values.

### Other secondary outcomes: safety important medical events (IME) adverse events (AE) and serious adverse events (SAE)

Important medical events (IMEs), adverse events (AEs) and serious adverse events (SAEs) are defined in the main trial protocol. These are expected to be rare occurrences. Since the trial participants are medically stable and living in the community, aphasia therapy is not expected to have an effect on these events. Therefore, no formal hypotheses have been stated about these outcomes. All IMEs, AEs and SAEs will be reported by the therapy group. As rare events, counts of IMEs, AEs and SAEs are expected to have a Poisson or negative binomial distribution. If the data suggests that there is a between-group difference of greater than 3 standard deviations in any of these event types, then the distributions of these events will be modelled, and appropriate generalised linear mixed models will be developed to assess differences between groups.

### Sensitivity analyses

Sensitivity analysis for the primary outcome will be conducted under various assumptions about the missing data. The main analysis is planned under an assumption of missing at random; therefore, the sensitivity of the results to plausible departures from MAR will be explored as a part of an intention-to-treat analysis strategy [25–27]. The 2010 National Research Council Panel on the Handling of Missing Data in Clinical Trials [27]. recommends a transparent and easily interpretable method for conducting a sensitivity analysis. Specifically, it recommends adding a parameter (delta) to the mean response. The parameter, delta, measures the degree of departure from missing at random. We propose using this approach to conduct a sensitivity analysis that assesses sensitivity of the results to plausible departures from the MAR assumption in the COMPARE trial. If the inference about the treatment effects can be overturned by plausible values of the delta parameter, then the results of the trial will be considered equivocal.

### Tables and figures for the Main paper

Table 1 will report the main baseline demographic, stroke characteristics. Table 2 will report baseline speech, language, and cognition measures by participant group. Table 3 will report key summary data about the therapy characteristics (e.g. amount of therapy, number of intervention levels passed, linguistic level reached) provided for each group. Tables 4 and 5 will report the primary and main secondary outcomes at immediate post intervention and 12 weeks follow-up and Table 6 will report deaths and Serious Adverse Events. Figure 1 will be the CONSORT diagram. Figure 2 will present a bar plot of the WAB-R-AQ at baseline, post intervention and 12-week follow-up for the three arms. Figures 3 and 4 will be a forest plot of the treatment effect on the primary outcome among different subgroups at therapy completion post stroke.

**Table 3 Tab3:** Intervention characteristics

	CIAT Plus *n* (%)	M-MAT *n* (%)	UC *n* (%)	All *n* (%)
Intervention compliant				
Intervention number of therapy hours, median (IQR)				
Length of sessions, mean no. minutes (SD)				
**Stimulus Set**				
Easy				
Moderate				
Hard				
**Intervention Levels progressed by final session**				
0				
1				
2				
3				
4				
5				
Number of speech therapy hours during follow-up period, median (IQR)

**Table 4 Tab4:** Outcomes immediately post intervention (mean, SD)

	CIAT Plus *n*	M-MAT *n*	UC *n*	All *n*
**Primary outcome measure**				
Western Aphasia Battery-Revised-Aphasia Quotient				
**Secondary outcome measures**				
Communication accuracy and efficiency				
No of CIUs				
% CIUs per minute				
COMPARE Naming Battery				
Communicative Effectiveness Index				
Scenario Test				
Stroke and Aphasia Quality of Life Scale				
Composite Score				
Energy				
Physical				
Communication				
Psychosocial

**Table 5 Tab5:** Outcomes at 12-week follow-up (mean, SD)

	CIAT Plus *n*	M-MAT *n*	UC *n*	All *n*
**Primary outcome measure**				
Western Aphasia Battery-Revised- Aphasia Quotient				
**Secondary outcome measures**				
Communication accuracy and efficiency				
No of CIUs				
% CIUs per minute				
COMPARE Naming Battery				
Communicative Effectiveness Index				
Scenario Test				
Stroke and Aphasia Quality of Life Scale				
Composite Score				
Energy				
Physical				
Communication				
Psychosocial

**Table 6 Tab6:** Adverse events and serious adverse events

	CIAT Plus *n*	M-MAT *n*	UC *n*	All *n*
Adverse events				
Deaths				
Serious adverse events				
0				
1				
2				
> 2

**Fig. 2 Fig2:**
[figure not shown]
Bar plot of WAB-R-AQ at baseline, post intervention and 12-week follow-up

**Fig. 3 Fig3:**
[figure not shown]
Forest plot of the treatment effect on the primary outcome for M-MAT and UC at therapy completion

**Fig. 4 Fig4:**
[figure not shown]
Forest plot of the treatment effect on the primary outcome for CIAT Plus and UC at therapy completion

### Summary

At the time of submission, 216 participants have been recruited and randomised in the study. The final follow-up data point was collected on July 23rd 2020, with data lock anticipated in September 2020.
